### Data collection

The participants had to complete the mental health questionnaires (DASS, HADS) on the moment (T1) after they signed the informed consent (T0) (figure 1) (table 1). At the same time a questionnaire had to be filled in about their satisfaction with the treatment of the OP (T1). This questionnaire was sent again to the participant by the researcher (DR) after their second consultation with the OP (T2) and after the last consultation with the OP, at the moment of full RTW (T3). If T2 and T3 happened at the same moment, T2 was considered as T3. The questionnaires were returned to the researcher after completion in pre-stamped envelopes. The same was done for the supervisors of the participants, who received a questionnaire about their treatment satisfaction at the same moments (T1, T2 and T3). The OP received for each participant after the moment of full RTW another questionnaire to assess their treatment satisfaction (T3).

Baseline characteristics of the participants such as gender, age, marital status, work characteristics (type of function, hours working, part/full time), sick leave data and costs of work incapacity of the participants were gathered from records of the police constabularies, the latter after one year follow-up. Data about direct costs of treatment and medication of the employee were obtained after one year follow up from the insurance company of the police, the DGVP.

Guideline adherence and the according performance were based on data of the medical files of the participant, gathered from the databases of the participating OHSs. The data of the medical files were made anonymous and were transferred to an Access database, to select the relevant data of the medical files.

### Study population: sample size and power analysis

In order to detect a relevant difference in survival analysis on our primary outcome return to work, nQuery Advisor [37] was used to calculate the sample size. Proportions used to determine the sample size needed, were analysed from sick leave data of the police constabularies in 1999. In 1999, 286 employees were registered as being on sick leave due to mental health problems, which was 6.6 % of the total sick leave registrations. Their duration of sick leave in 1999 was 35.5 % of the total volume of sick leave, with an average of three months per case. With a power of 90%, at a 0.05 level, a two-sided log-rank test for equality of survival curves was done, assuming a difference between the intervention and control group proportion still on sick leave after one year of 0.25. This test indicated that a sample size was needed of 107 in each group. Assuming a dropout rate of 20%, inclusion of a total of 268 patients was necessary to statistically detect a clinically relevant difference.

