### Data analysis

All analyses will be conducted according to the intention-to-treat principle and will be performed on the patient level. To examine the success of randomization, descriptive statistics will be used to compare the baseline measurements of the two groups. If necessary, analyses will be adjusted for prognostic dissimilarities.

The evaluations on the effectiveness of the guideline compared to usual care will be performed with two tailed tests at a significance level of 5% (P < 0.05). To examine differences in the data on RTW, we will use Kaplan Meier's and the Cox proportional hazard regression for recurrent events. The general idea behind this analysis is that the different time periods are analysed separately adjusted for the fact that the time periods within one patient are dependent. Recurrences of sick leave for any reason during follow-up will be added to the Cox proportional hazards model with the time to event approach, in which only the transitions from no treatment success (sick leave) to treatment success (full RTW) are taken into account [38].  In this model, the state of sick leave until the moment of inclusion will be added as a covariate. Number and days of sick leave periods in the year before inclusion will be added as a potential effect-modifier.

In a linear regression model treatment satisfaction during treatment (T2) and after treatment by the OP (T3) will be measured as respectively a short term and a long term effect and differences will be compared between the groups. Treatment satisfaction at the start of the treatment (T1) will be added as a covariate, even as the treatment group to examine differences in effects between the groups. The levels of treatment satisfaction of both the employees and their supervisors will be compared for the different moments with a chi-square test. Pair-wise correlations will be used to compare treatment satisfaction of the employee and their supervisor on the different moments.

In the Cox and linear regression models potential treatment differences by the OPs and their OHSs will be taken into account by means of nested dummy variables. The police constabulary the employee works for, will be put into the model as a binomial variable. Differences in sick leave patterns in the year before inclusion and in the severity of the mental health problems (DASS/HADS-scores) will be put into the model as potential effect modifiers.

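### The sample-size paragraph is internally inconsistent: 107 per group does not follow from a 0.25 difference at 90% power, and that difference fits poorly with the stated three-month average duration

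*Protocol article*

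**What the plan says.** All the figures stand in the protocol article under *Study population: sample size and power analysis*.

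- Source of the proportions: "Proportions used to determine the sample size needed, were analysed from sick leave data of the police constabularies in 1999". The two proportions themselves are not printed.
- Source duration: "Their duration of sick leave in 1999 was 35.5 % of the total volume of sick leave, with an average of three months per case".
- Test and error rates: "With a power of 90%, at a 0.05 level, a two-sided log-rank test for equality of survival curves was done". The *Data analysis* section also uses two-sided tests at 5%.
- Effect: "assuming a difference between the intervention and control group proportion still on sick leave after one year of 0.25".
- Result: "This test indicated that a sample size was needed of 107 in each group". A 20% dropout allowance is then added, giving 268 in total.

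**The concern.** A log-rank sample size for a fixed absolute difference depends on where the two proportions lie, and here they are not given. The calculation can still be checked, because the sample size has a maximum over all possible base rates, and 107 lies above it.

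The effect itself is also hard to square with the source data. An average absence of about three months leaves few people absent at twelve months, so there is little room for a 25-point reduction at that time.

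This paragraph is the only power justification for the primary outcome, and it presents 268 as the number needed to detect a clinically relevant difference. As printed, a reader cannot tell which effect the trial was sized for. A neutral result could then be taken to rule out effects that the trial was not built to detect.

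**Working it through.** **Inputs.** Two-sided alpha 0.05, power 90%, log-rank test, difference 0.25 at one year, 20% dropout, and a three-month average are all from the sample-size section. Equal allocation is assumed from the equal group sizes. The base proportions are not printed, so the whole range was scanned.

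**1. Dropout step.** 107/0.8 = 133.75, so 134 per group and 268 in total. This reproduces.

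**2. The 107.** Let p1 be the lower proportion still absent at one year and p2 = p1 + 0.25 the higher. The return-to-work hazard ratio is HR = ln(p1)/ln(p2), and (1.960 + 1.282)² = 10.51.

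- Freedman events: 10.51 × ((HR + 1)/(HR − 1))²
- Schoenfeld events: 4 × 10.51/(ln HR)²
- n per group = events/(2 − p1 − p2)

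Example at 0.40 vs 0.65: HR = 0.916/0.431 = 2.127. Freedman events = 10.51 × (3.127/1.127)² = 80.9, and 80.9/0.95 = 85.1 per group. Schoenfeld gives 73.8/0.95 = 77.7.

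| p1 vs p2 | Freedman n | Schoenfeld n | Proportions, continuity-corrected |
|---|---|---|---|
| 0.01 vs 0.26 | 20.3 | 16.1 | 45 |
| 0.10 vs 0.35 | 48.5 | 44.0 | 65 |
| 0.25 vs 0.50 | 75.7 | 70.0 | 85 |
| 0.40 vs 0.65 | 85.1 | 77.7 | 90 |
| 0.50 vs 0.75 | 82.0 | 72.5 | 85 |
| 0.60 vs 0.85 | 71.4 | 58.3 | 73 |

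The maximum over all base rates is 85.2, so 86 (Freedman, near 0.41 vs 0.66), 78 (Schoenfeld) and 90 (continuity-corrected). None reaches 107. By Freedman's formula, 107 corresponds to a difference of about 0.22 or less.

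**3. Direction of the error.** With 107 per group at 0.40 vs 0.65, events = 107 × 0.95 = 101.7. The normal deviate for power is √101.7 × 1.127/3.127 − 1.960 = 1.67, which is about 95% power. This is close to the minimum over base rates; elsewhere the power is higher.

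**4. A possible origin of 107.** 85.2/0.8 = 106.5, which rounds up to 107. Freedman's n divided by 0.8 rounds up to exactly 107 for lower proportions of 0.377 to 0.439.

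**5. The three-month average.** If it is mean completed duration, Markov's bound gives P(absent beyond 12 months) ≤ 3/12 = 0.25. Particular shapes with mean 3 months, which are assumptions, give less: exponential exp(−12/3) = 1.8%, Weibull at most 6.0%, lognormal at most 4.8%.

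**6. If the average counts only days within 1999.** With onsets spread evenly over the year (assumption), a case that does not return contributes about 6 in-year months. A mixture of 40% such cases and 60% averaging one month gives 0.4 × 6 + 0.6 × 1 = 3.0 months, so 0.40 vs 0.15 becomes possible. The ceiling among registered cases is then 3/6 = 0.50. At 0.50 vs 0.25 the Freedman n is 76, or 95 with dropout included, which is still not 107.

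**7. Detectable effect.** HR = exp(2 × 3.2415/√D), where D is the number of returns to work. Take 214 analysed (2 × 107) or 200 (80% of the 250 envelopes described under *Randomisation*), with 94% to 98% returning within the year (an assumption, from step 5).

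- D = 200 × 0.94 = 188: HR = 1.60
- D = 214 × 0.98 = 209.7: HR = 1.56

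Under proportional hazards the one-year gap is then 0.06 − 0.06^1.60 = 0.049 at one end and 0.018 − 0.018^1.56 = 0.016 at the other.

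**The case against.** The strongest reply is that a reader might infer that a 0.25 difference cannot occur, and the document does not establish this. Markov's bound needs the mean completed duration in the trial population. The article gives an average for duration in 1999, which may be cut off at the calendar year. It covers all registered cases, whereas the trial enrols only people still absent at the consultation with the occupational physician. Both points allow a heavier one-year tail. Among people absent beyond two weeks, ordinary lognormal shapes with a three-month overall mean give 3% to 7%, and extreme shapes up to about 20%. This objection stands: 0.25 is poorly supported, not impossible.

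A reader might also infer that the trial is underpowered, or that the 90% has no basis. The mismatch in n points the other way, since under the plan's own effect 107 per group gives more than 90% power. Log-rank power depends on the hazard ratio and the number of events, so the trial may be adequately powered for a hazard ratio that the article does not state.

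Two further points stand. Double-counted dropout is conjecture: it needs about 0.40 vs 0.65, which sits even less well with a three-month average. The hazard ratio of about 1.6 rests on an assumed event proportion and a single-event log-rank test, while the *Data analysis* section plans a Cox model for recurrent events.

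A condensed article may leave the two base proportions to a fuller document. That does not answer the point, because the figures it does print fail to agree at any base rate.

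**Conclusion.** The paragraph is internally inconsistent and should be corrected.

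- The pre-dropout 107, and the 268 built on it, do not follow from the printed inputs. The required number is at most 86 per group (Freedman), which 20% dropout turns into 108 per group (86/0.8 = 107.5), or 216 in total. This holds at every base rate and needs no distributional assumption beyond proportional hazards. The discrepancy is conservative.
- The 0.25 difference fits poorly with the three-month average. On the completed-duration reading it requires the control group at the 25% ceiling and the intervention group at zero. On the in-year reading, or after allowing for selection at enrolment, a larger tail is possible, but nothing in the article shows it.

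The 2% to 6% tail and the hazard ratio of 1.56 to 1.60 are illustrations under stated assumptions, not figures from the plan. The endpoint, randomisation and analysis are unaffected. The point should be fixed, but it does not threaten the trial's validity.

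**What to change.** Rewrite the sample-size paragraph so that it:

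1. gives the two one-year proportions actually used and the hazard ratio they imply;
2. says whether three months is completed duration or days within 1999 and, if the latter, gives the one-year proportion from uncut spells;
3. says whether 107 already includes dropout, and corrects 107 and 268, or the stated power, so that they follow from the inputs;
4. states the detectable effect as a return-to-work hazard ratio with its assumed event proportion, for example about 1.56 to 1.60 at 90% power if 200 to 214 are analysed and 94% to 98% return within the year.

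The cost is one restated paragraph and a look back at the 1999 data and the original software input. No extra recruitment is needed. The restated effect may look less favourable than 25 points, but readers will then know what a neutral result can and cannot exclude.

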### Data analysis

All analyses will be conducted according to the intention-to-treat principle and will be performed on the patient level. To examine the success of randomization, descriptive statistics will be used to compare the baseline measurements of the two groups. If necessary, analyses will be adjusted for prognostic dissimilarities.

The evaluations on the effectiveness of the guideline compared to usual care will be performed with two tailed tests at a significance level of 5% (P < 0.05). To examine differences in the data on RTW, we will use Kaplan Meier's and the Cox proportional hazard regression for recurrent events. The general idea behind this analysis is that the different time periods are analysed separately adjusted for the fact that the time periods within one patient are dependent. Recurrences of sick leave for any reason during follow-up will be added to the Cox proportional hazards model with the time to event approach, in which only the transitions from no treatment success (sick leave) to treatment success (full RTW) are taken into account [38].  In this model, the state of sick leave until the moment of inclusion will be added as a covariate. Number and days of sick leave periods in the year before inclusion will be added as a potential effect-modifier.

In a linear regression model treatment satisfaction during treatment (T2) and after treatment by the OP (T3) will be measured as respectively a short term and a long term effect and differences will be compared between the groups. Treatment satisfaction at the start of the treatment (T1) will be added as a covariate, even as the treatment group to examine differences in effects between the groups. The levels of treatment satisfaction of both the employees and their supervisors will be compared for the different moments with a chi-square test. Pair-wise correlations will be used to compare treatment satisfaction of the employee and their supervisor on the different moments.

In the Cox and linear regression models potential treatment differences by the OPs and their OHSs will be taken into account by means of nested dummy variables. The police constabulary the employee works for, will be put into the model as a binomial variable. Differences in sick leave patterns in the year before inclusion and in the severity of the mental health problems (DASS/HADS-scores) will be put into the model as potential effect modifiers.

To assess whether protocol deviations will cause bias, the results of the intention-to-treat analyses will be compared to per-protocol analyses. A process evaluation will be done, based on the assessment of guideline adherence by means of performance indicators [18]. For each performance indicator potential effects on our primary outcomes will be measured.

Indirect costs can be calculated using the friction cost approach (friction period 122 days) and the human capital approach, based on income as provided by the employer or as derived from function, age and gender [30]. Bootstrapping will be used for pair wise comparison of the mean groups to calculate mean differences and confidence intervals in costs and cost-effectiveness ratios for all interventions. All these analyses will be conducted in SPSS 14.0, Excel and, if necessary, in Strata.

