**Methods/Design:**

In a randomized controlled trial (RCT), subjects in the intervention group were treated according to the guideline. The control group received usual care, with minimal involvement of the OP and easy access to a psychologist. Subjects were recruited from two Dutch police departments. The primary outcomes of the study are return to work and treatment satisfaction by the employee, employer, and OP. A secondary outcome is cost-effectiveness of the intervention, compared with usual care. Furthermore, prognostic measures are taken into account as potential confounders. A process evaluation will be done by means of performance indicators, based on the guideline.

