**Figure 2 F2:**
[figure not shown]
Timeline of measured sick leave data of a potential participant.

The primary outcome measure described in our study is full RTW: i.e. duration of sick leave due to mental health problems in calendar days from the first day of sick leave to full return to work in own or equal earnings (table 1). In addition, the net return to work to own or equal work was measured. This is the net duration of sick leave due to mental health problems in hours of full work absenteeism from the first day of sick leave to full return to work with own or equal earnings. The difference with full RTW is that the hours of partial return to work and % contract working hours (36 hours = 100%) are converted into the number of hours of full work absenteeism [23]. This may result in a more precise measure of RTW, when compared to full RTW. As figure 2 shows, net and full RTW consider the time period between T0 and T3, in which data collection by questionnaires took place (figure 1).

**Table 1 T1:** Measured data and their instruments and timing of data collection

**Data**	**Instrument**	**Base-line**	**Follow up**			
**Data related to primary outcomes**		**T0**	**T1**	**T2**	**T3**	**T4**
Return to work						
Full Return to work	Database company	X			X	
Net return to work	Database company	X			X	
First (partial or full) return to work	Database company	X	X	X	X	
Time until 1^st ^recurrence	Database company	X				X
Number and days of recurrences of sick leave	Database company				X	X
Total days of sick leave during one year follow up	Database company	X			X	X
Treatment satisfaction						
Treatment satisfaction of employee	Questionnaire		X	X	X	
Treatment satisfaction of employer	Questionnaire		X	X	X	
Treatment satisfaction of the OP	Questionnaire				X	

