**Data related to prognostic measures**						

I) Personal characteristics						
Gender, Age	Database company	X				
Severity disorder: DASS/HADS (effect modifier)	Questionnaires		X			
Work-relatedness of the disorder	Medical files OHS	X				
Sick leave in year before inclusion (effect modifier)	Database company	X				
II) Treatment						
Treating occupational physician (OP)	Medical files OHS	X				
Diagnosis made by the OP	Medical files OHS	X				
Guideline adherence of the OP	Medical files OHS	X	X	X	X	
III) Work characteristics						
Type of function	Database company	X				
Number of working hours	Database company	X				
Police constabulary	Database company	X				

Another primary outcome variable that is part of the RTW process is first RTW: i.e. the duration of sick leave due to mental health problems in calendar days to first (partial or full) return to own or equal work. Other variables are related to recurrences of sick leave periods in the one year follow-up (T4)(table 1). These variables are the time in calendar days until the first recurrence of sick leave takes place and the number of and days during recurrences [21]. Total days of sick leave during follow-up is a primary outcome variables as well.

There was double registration of sick leave data, as both the employer and the OHS have their own registration system. The aim was to compare data of both systems, with the sick leave data of the employer as the 'golden standard'. This additional effort was done as reliable sick leave data are hard to get, since there is a known discrepancy with self-reported sick leave [24,25].

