#### Treatment satisfaction

Treatment satisfaction is a relevant outcome measure in occupational health care and therefore another primary outcome [26]. Higher patient satisfaction is related to better patient compliance and can improve the quality of OHSs. To date, most researchers assume that patient satisfaction is best defined as a patient's evaluation of aspects of a health care service based on the fulfilment of patient expectations. Since patients, employers and health care providers (OPs) are all involved stakeholders in the RTW process, it is important to measure the treatment satisfaction of all of these stakeholders.

Patient and employer satisfaction were measured using a short version of the Patient Satisfaction with Occupational Health Professionals Questionnaire [26]. This questionnaire was designed specifically for measuring satisfaction with occupational health care. It was designed in previous research on the quality of rehabilitation of cancer survivors [27] and transferred to occupational health care in another study on employees with mental health problems [18]. The 13 items of this questionnaire refer to (a) satisfaction in general (2 items), (b) interpersonal approach (4 items), (c) communication manner (2 items), (d) professional knowledge (5 items), and (e) total satisfaction of the treatment by the OP (13 items). Respondents answered on thirteen statements on a 5-point Likert scale: 'totally disagree – disagree – no opinion – agree – totally agree' (table 2). Because a higher score indicates more treatment satisfaction, item 3,4,9,10 and 12 will be recoded. The patient satisfaction questionnaire was adapted to the situation of the employer, to measure the treatment satisfaction of the supervisor (table 3).

**Table 2 T2:** Treatment satisfaction questionnaire employee

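### The article contradicts itself on which outcomes are primary and tests all of them at a flat 5% with no hierarchy or success rule

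*Protocol article*

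**What the plan says.** All statements are in the Protocol article.

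- **Abstract, Methods/Design:** "The primary outcomes of the study are return to work and treatment satisfaction by the employee, employer, and OP".
- **Primary outcomes, Return to work:** "The primary outcome measure described in our study is full RTW". Net RTW follows as an addition: "In addition, the net return to work to own or equal work was measured".
- **Same subsection, after Table 1:** "Another primary outcome variable that is part of the RTW process is first RTW". Recurrence measures come next: "Other variables are related to recurrences of sick leave periods in the one year follow-up (T4)". Then: "Total days of sick leave during follow-up is a primary outcome variables as well".
- **Treatment satisfaction:** "Treatment satisfaction is a relevant outcome measure in occupational health care and therefore another primary outcome".
- **Table 1:** six RTW rows and three satisfaction rows stand under the heading for data related to primary outcomes.
- **Sample size and power analysis:** a two-sided log-rank test on return to work at 0.05 with 90% power, giving 107 per group and 268 in total. Satisfaction plays no part.
- **Data analysis:** evaluations of effectiveness are "performed with two tailed tests at a significance level of 5% (P < 0.05)". RTW is to be analysed with Kaplan-Meier and a Cox model for recurrent events that counts transitions from sick leave to full RTW. Satisfaction is to be compared between groups by linear regression at T2 and T3, with the T1 score as covariate.

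**The concern.** Full RTW is introduced in the singular as the primary measure, yet the same section and the abstract give primary status to several others. Nothing says which result decides the trial, whether all must succeed, or whether one is enough. Read literally, a significant difference on any of them at 5% could be reported as meeting a primary outcome.

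Two features add weight. The sample size was justified for RTW only, so the other declared primaries have no stated power. Participants, employers and OPs were not blinded, so the satisfaction ratings are the outcomes most open to bias, yet one of them alone could carry a primary claim.

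**Working it through.** **The plan's own figure.** The article states no familywise error rate, so there is none to reproduce. The nearest related figure is the total sample size: 2 × 107 / (1 − 0.20) = 267.5, rounded up to 268, which agrees with the article.

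**Inputs from the article.** Alpha is 0.05 two-sided per test. The number of tests k can be counted in three ways:

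- *Between-group tests that Data analysis describes:* one Cox model, employee satisfaction at T2 and T3, supervisor satisfaction at T2 and T3. 1 + 2 + 2 = 5.
- *One test per declared primary:* three RTW measures (full, first, total days) and three stakeholders. 3 + 3 = 6.
- *Every declared primary with its time points:* three RTW measures, employee T2/T3, supervisor T2/T3, OP at T3. 3 + 2 + 2 + 1 = 8.

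**Input not in the article.** The correlation ρ between test statistics is assumed, and a range is shown.

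**Formulas.** For independent tests, the chance of at least one false positive when no effect exists is 1 − 0.95^k:

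- k = 5: 1 − 0.95^5 = 0.226
- k = 6: 1 − 0.95^6 = 0.265
- k = 8: 1 − 0.95^8 = 0.337

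For a common correlation ρ, with c = 1.96, φ and Φ the standard normal density and distribution function, and s the shared component, the chance is

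1 − ∫ φ(s) [Φ((c − s√ρ)/√(1−ρ)) − Φ((−c − s√ρ)/√(1−ρ))]^k ds.

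| k | ρ = 0 | ρ = 0.3 | ρ = 0.5 | ρ = 0.7 | ρ = 0.9 |
|---|---|---|---|---|---|
| 5 | 22.6% | 20.9% | 18.3% | 14.8% | 10.2% |
| 6 | 26.5% | 24.1% | 20.7% | 16.4% | 10.8% |
| 8 | 33.7% | 30.0% | 25.0% | 19.1% | 11.9% |

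A single common correlation is crude, because RTW measures should correlate more with each other than with satisfaction. Simulating eight tests in two blocks (three RTW at 0.5-0.9, five satisfaction at 0.3-0.7, between blocks 0-0.2) gives 22-31%.

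**After the fix.** One primary test at 0.05 has a 5% error rate by construction. Holm's procedure keeps the familywise rate at or below 5% whatever the correlation. With six tests its strictest step is 0.05/6 = 0.0083. The article gives the 0.25 difference but no base rate, so I took 0.65 against 0.40 still on sick leave, close to the least favourable pair for that difference. With the Freedman log-rank formula and 107 per group:

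- h = ln 0.40 / ln 0.65 = 2.127
- z = √(107 × (2 − 0.65 − 0.40)) × (h − 1)/(h + 1) = 10.08 × 0.3604 = 3.63
- power at 0.05: Φ(3.63 − 1.96) = 95%
- power at 0.0083: Φ(3.63 − 2.64) = 84%

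The 95% differs from the article's 90%. That is a separate question about how 107 was obtained, and the error rates above do not depend on it.

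**The case against.** A reader might infer that at least eight comparisons are each tested at 5%, so that an error rate of 20-34% is established. The article does not support that.

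- **Count.** No separate test is named for first RTW or total sick-leave days, and recurrences are folded into the one Cox model. The satisfaction regression needs a T1 covariate and outcomes at T2 and T3, so it does not fit OP satisfaction, which is collected only at T3. Where T2 and T3 coincide, they are treated as one assessment. In the other direction, chi-square comparisons of satisfaction levels are also planned. The number of tests is therefore uncertain both ways.
- **Size.** A lower end of about 20% is just the eight-test value near ρ = 0.7. At 0.9 it is 12%.
- **Error rate.** A reader might also infer that the stated 5% is false. It is a per-test level. The article makes no claim that any one success suffices, and Study design sets out RTW and satisfaction as separate hypotheses. Whether to adjust across distinct questions is partly a matter of judgement, and a multiplicity rule may stand in an analysis plan that is not shown.

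These points limit the count and the precision, and they stand. They do not remove the defect. The conflicting labels are in this article, and an analysis plan would first have to settle which of them holds. Treating RTW and satisfaction as separate families still leaves 1 − 0.95^3 = 14.3% for three independent RTW tests and 22.6% for five independent satisfaction tests. Nor can full RTW simply be taken as the sole primary, since the abstract and two later statements say otherwise.

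**Conclusion.** The point holds in this form: the article is inconsistent on what is primary, and its flat 5% level comes with no hierarchy or success rule. If any one significant primary result is read as success, the false-positive chance is about 23-34% for five to eight independent tests, 15-19% at correlation 0.7 and 10-12% at 0.9. It is at least twice the nominal 5% throughout that range. The figures rest on three assumptions: the any-one-suffices reading, which the article neither states nor rules out; the count of tests; and the correlations. The direction is firm and the exact size is not. It should be corrected before the analysis.

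**What to change.** Before unblinding, and in a dated decision, reconcile the abstract, the two RTW statements and the satisfaction statement in one of two ways.

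1. **Preferred.** Name time to full RTW as the single primary outcome at two-sided 0.05, and name one primary test: either the log-rank test of the sample-size section or the Cox model of Data analysis. The sample-size section speaks of return to work without saying full RTW, so state that link too. Make first and net RTW, total sick-leave days, recurrences and all satisfaction measures secondary.
2. **If the declared primaries must stay.** Fix one test per RTW measure and one per stakeholder, with its time point. For the OP, also choose between or combine the two satisfaction ratings in Table 4. Apply Holm's procedure across that set.

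The cost is more than re-labelling. Recruitment ended in January 2005, so the change alters published primary outcomes after enrolment closed and must be reported as such. The article says the researchers were blinded to allocation, which is what would make a late decision defensible. Under option 1 the other measures can no longer carry a primary claim alone. Under option 2 some power is lost: about 84% instead of 95% for RTW at Holm's strictest step, under the base rates assumed above.
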